**Design:**

VINCI-AD is an investigator-led, single-site, single-blind, sham-controlled crossover pilot study which aims to assess the safety and feasibility of tVNS in 40 participants with amnestic MCI. All participants will attend for three consecutive study visits during which they will be randomised to receive no stimulation (baseline), active tVNS stimulation (stimulation at cymba conchae of left ear) or sham tVNS stimulation (at earlobe). Safety will be primarily assessed by ascertainment of adverse events. Further safety assessment will examine the impact of acute tVNS on subjective (orthostatic symptoms), peripheral (finometry-based blood pressure) and central (assessed via Near Infrared Spectroscopy [NIRS]) haemodynamic responses to active stand. Feasibility will be determined using a custom-designed occupational assessment of device usability. Exploratory secondary analysis in VINCI-AD will examine the potential impact of acute tVNS on associative memory, spatial memory and inhibitory control to inform sample size estimates for future trials of tVNS in older adults with MCI.

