## Methods/design

### Study design

VINCI-AD is a single-site, single-blind, sham-controlled crossover pilot study in patients with amnestic MCI. Each participant is assessed at baseline (no stimulation) followed by randomisation to both sham stimulation and active tVNS stimulation over two subsequent study visits. The study comprises a baseline assessment (visit 1) followed 7–10 days later by either an active or sham stimulation study visit and again 7–10 days later by a third visit wherein the final condition (active or sham) will be undertaken. The inclusion of a sham stimulation condition is to confound for potential unblinding, which is common in device trials. Participants will be enrolled and consented by study clinician (HD). Please see Fig. 1 for an illustration of randomisation and sham stimulation technique.

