### Randomisation

Patients who provide informed consent to participate and who fulfil eligibility criteria will be enrolled into the study. Initial visit (visit 1) involves baseline assessments of neurocardiovascular, cognitive, and inflammatory status. Participants are then randomised to either active or sham stimulation condition at the following visit and then to the alternate condition at the final visit. Participants are blinded to the active or sham stimulation condition but study researchers are not (i.e. single-blinded). Please see Fig. 1 for randomisation strategy.

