### Sample size

To establish the safety and feasibility of tVNS in a population of older adults with MCI, VINCI-AD aims to recruit 40 participants for inclusion. This sample size is based on previous literature which investigated the effects of tVNS in healthy young adults [19–21, 23, 55] and also CU older adults [47]. Potential effect sizes from the results of this feasibility study will inform an accurate power calculation for future definitive trials.

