### Statistical analysis

VINCI-AD will assess the safety and feasibility of tVNS in older adults with MCI. All participants will be included in final analysis in an “intention-to-treat” fashion. Statistical analysis will be conducted using MATLAB (The MathWorks, Inc., Natick, MA, USA), SPSS (IBM SPSS Statistics for Windows, Armonk, NY: IBM Corp) and GraphPad Prism (GraphPad Software, Inc., San Diego, CA, USA). We anticipate that TSI analysis will require cleaning to remove “noisy” channels i.e. removing large spikes (changes in oxy-Hb larger than 0.5 mM/mm in amplitude); noisy channels will be excluded from analyses and data analyses will utilise software Platform for Optical Topography Analysis Tools [56] with a bandpass filter with cut-off frequencies of 0.01–0.8 Hz to remove instrumental or physiological noise [57].

In the first instance, descriptive statistics will be described for the cohort, reported as means (with standard deviations) or medians (with inter-quartile ranges) and proportions (percentages) as appropriate.

The primary aim of the current study is to assess the safety and feasibility of tVNS in MCI. To assess safety, a chi-square test will compare the number of adverse events reported during the active vs. sham condition. Further safety assessment will elicit symptoms experienced during active stand (using a chi-square statistic), peripheral (beat-to-beat blood pressure response to orthostasis – using mixed-effects linear regression with study condition as the independent variable, with random intercepts for study participant) and central (TSI – also assessed using a linear mixed-effects model). Feasibility will be reported via recruitment rates, successful enrolment, and study completion in proportions and percentages. Tolerability will be assessed using Likert scales, which will be compared between active and sham conditions using paired between-condition statistics (t-test if normally distributed or non-parametric equivalent). Descriptive statistics will be used to report acceptability using the modified Kettle test.

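### Adverse events and active-stand symptoms are to be compared by an ordinary chi-square test although the same participants supply the data under each condition, so the error rate is not the nominal one

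*Protocol article*

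**What the plan says.** All of this is in the protocol article.

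- **Design.** Study design: "VINCI-AD is a single-site, single-blind, sham-controlled crossover pilot study in patients with amnestic MCI". After a baseline visit without stimulation, each person has both conditions. Randomisation: "Participants are then randomised to either active or sham stimulation condition at the following visit and then to the alternate condition at the final visit".
- **Size.** Sample size: "VINCI-AD aims to recruit 40 participants for inclusion". The number is taken from earlier studies. No significance level, power, event rate or correlation is given for any safety comparison.
- **Standing of the outcome.** Abstract, Design: "Safety will be primarily assessed by ascertainment of adverse events".
- **Tests.** Statistical analysis: "To assess safety, a chi-square test will compare the number of adverse events reported during the active vs. sham condition". The next sentence adds "symptoms experienced during active stand (using a chi-square statistic" to the further safety assessment. Table 1 schedules the active stand at all three visits.
- **Neighbouring analyses.** The same paragraph gives beat-to-beat blood pressure a mixed model with a participant-level random intercept, cerebral oxygenation (TSI) a linear mixed model, and the Likert scales a paired test of active against sham.

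**The concern.** An ordinary chi-square test treats the active and sham records as coming from different people. Here they come from the same people, and someone who reports reactions at one visit is likely to report them at the other. The test ignores that covariance and so uses the wrong variance for the difference.

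The wording adds a second problem. It compares numbers of events, not numbers of people with an event. The section on safety and tolerability lists several common reactions (tingling, burning, redness, itching, tinnitus, headache), so one person at one visit can contribute several events that are not independent of each other.

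The two problems push in opposite directions. Ignored pairing makes the test too cautious, which in a safety comparison means that harm is more easily overlooked. Clustering of events within a visit makes it too ready to reject. A reader of the result could not tell which had prevailed.

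**Working it through.** The plan gives no figure to reproduce for this comparison, so the check asks what error rate the stated test would have.

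**Inputs**
- n = 40 pairs (Sample size section), with no missing data assumed.
- p = 18% affected per condition. This is the upper figure for common reactions in the section on safety and tolerability. It comes from published data and is not a planning rate for this trial.
- Assumed: two-sided 5% level; within-person correlation φ from 0 to 0.7; active rate of 40% or 36% for power; 1, 2 or 3 events, equally likely, per affected person-visit.

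**1. Participant level (any event, yes/no)**

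The probability of an event under both conditions is p11 = p² + φp(1−p). The difference in proportions has true variance 2p(1−p)(1−φ)/n, while the chi-square test assumes 2p(1−p)/n. In large samples:

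size ≈ 2[1 − Φ(1.96/√(1−φ))]

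At φ = 0.5 this is 2[1 − Φ(2.77)] = 0.6%. Results with n = 40 and p = 18%:

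| φ | chi-square, large-sample formula | chi-square, n = 40 | exact McNemar | mid-p McNemar |
|---|---|---|---|---|
| 0 | 5.0% | 5.2% | 2.4% | 4.3% |
| 0.2 | 2.8% | 3.1% | 2.1% | 4.1% |
| 0.3 | 1.9% | 2.1–2.2% | 1.9% | 3.9% |
| 0.5 | 0.6% | 0.8% | 1.2% | 3.1% |
| 0.7 | 0.03% | 0.1% | 0.3% | 1.3% |

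Exact McNemar is conservative because few pairs disagree. At φ = 0.5, p11 = 0.0324 + 0.5 × 0.1476 = 0.1062, so about 40 × 2 × (0.18 − 0.1062) = 5.9 discordant pairs are expected. With six, all must point the same way (2 × 0.5⁶ = 0.031).

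A negative correlation, which is less plausible, raises the chi-square size: about 7.5% at φ = −0.2.

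**2. Power at participant level**

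| active vs sham | φ | chi-square | exact McNemar | mid-p McNemar |
|---|---|---|---|---|
| 40% vs 18% | 0.2 | 60% | 58% | 67% |
| 40% vs 18% | 0.5 | 62% | 81% | 89% |
| 36% vs 18% | 0.2 | 44% | 41% | 50% |
| 36% vs 18% | 0.5 | 41% | 60% | 71% |

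For 40% vs 18% the largest possible φ is √(0.18 × 0.60 / (0.40 × 0.82)) = 0.57, so the φ = 0.5 rows are favourable to the paired tests.

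**3. Event level**

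With totals A and S, the test (A−S)²/(A+S) assumes Var(A−S) = E(A+S). With 1 to 3 events per affected visit (mean 2, mean square 14/3), the ratio of true to assumed variance is

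[(14/3)p − 4·p11] / (2p)

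and size ≈ 2[1 − Φ(1.96/√ratio)].

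| φ | p11 | ratio | formula | simulated, n = 40 |
|---|---|---|---|---|
| 0 | 0.0324 | 1.97 | 16% | 17% |
| 0.3 | 0.0767 | 1.48 | 11% | 11% |
| 0.5 | 0.1062 | 1.15 | 7% | 7% |
| 0.7 | 0.1357 | 0.83 | 3% | 4% |

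The ratio equals 1 when p11 = (2/3)p = 0.12, that is at φ = (0.12 − 0.0324)/0.1476 = 0.59. Below that the test is liberal, above it conservative.

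**4. Stand symptoms**

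If all three visits are compared at 18%, simulated chi-square size is 2.4%, 0.9% and 0.1% at intraclass correlations of 0.2, 0.4 and 0.6. Cochran's Q gives 5.1%, 5.3% and 4.6%.

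**The case against.** **McNemar may be meant.** Its statistic is referred to a chi-square distribution, so the wording could be shorthand. This is not the natural reading. The same paragraph marks within-person methods where it intends them, and McNemar's test cannot be applied to counts of events.

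**Other safety analyses are sound.** A reader might infer that primary safety rests on this one invalid test. The documents do not support that. Table 1 places the active stand with TSI under primary safety, and blood pressure and TSI get mixed models. The section on safety and tolerability also lists Likert questionnaires on pain, skin discomfort, tingling, headache and tinnitus, and Likert scales are compared by paired tests. Chi-square is only the sole stated test of adverse-event reports. This objection stands and limits the point.

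**A conservative test raises no false alarm.** True at participant level when the correlation is positive, and at zero correlation the test is about nominal. It is therefore too strong to say that every p-value would mislead, or that event counting always inflates the error: the 17% belongs to zero correlation and the direction reverses at high correlation.

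**The remedy may gain little.** This stands for exact McNemar, which is itself conservative and has no more power than chi-square at φ = 0.2. It does not stand for the mid-p version.

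**It is a pilot.** No level, power or decision rule is attached to the test, and a paired analysis remains possible later. That lowers the stakes, but the article commits to this test for its lead safety measure. Since the test is named, it is not a detail left to an analysis plan.

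**Conclusion.** The point holds in a limited form. The stated test for adverse events, and that for stand symptoms, assumes independence that a crossover does not provide, and its error rate equals the nominal one only by coincidence of the correlation and the counting rule.

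On yes/no data with positive correlation the consequence is a conservative test and lost power to see harm. Against mid-p McNemar, for 40% vs 18%, the loss runs from about 7 points (φ = 0.2) to 27 points (φ = 0.5). On event totals the false-positive rate could lie anywhere from about 4% to 17% over the range examined.

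These sizes rest on assumed correlations, event multiplicity, active rates and a 5% level, none of which the article gives, and on a published upper rate used as an illustration. The failure of independence does not rest on them. It follows from the design and the named test.

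**What to change.** In the Statistical analysis section:

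1. Define the outcome per participant and condition as at least one adverse event, yes or no.
2. Compare active with sham by mid-p McNemar, or by a conditional or mixed logistic model. Give a 95% confidence interval for the paired risk difference. Prefer these to exact McNemar, which is conservative at this size.
3. State which conditions the symptom comparison covers. The safety section introduces it under active and sham stimulation, but Table 1 has the stand at every visit. For active against sham, use the same paired test. For all three visits, use Cochran's Q or a logistic model clustered on participant.
4. Report event counts descriptively, or with a count model clustered on participant.

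The cost is a few lines of text. No new data, visits or participants are needed, because records are already made for each person under each condition.

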### Safety and tolerability of tVNS in MCI

The risk associated with use of the NEMOS © Cerbomed tVNS device is minimal as published data of the safety profile shows minimal adverse events. The most common adverse events reported include local skin tingling, burning, redness, itching, tinnitus or headache which occur in up to 18% of participants, and tends to resolve quickly after discontinuation of the use of the device [42]. Due to the theoretical risk of increasing cardiac vagal-mediated bradycardias or hypotensive episodes by stimulating the right VN, participants will have stimulation of the left ear only.

During the active and sham stimulation conditions, safety will be recorded by completion of the following:

Contemporaneous recording of any adverse events reported by participants whilst undergoing either active or sham stimulation.Likert-Based Questionnaires (See Additional File 2) will assess for established side effects previously reported with tVNS: pain, skin discomfort, tingling, headache and tinnitus. These will be administered both during active and sham stimulation.Detailed assessment of subjective (OH symptoms including faintness, light-headedness), peripheral (beat-to-beat blood pressure) and central (TSI) haemodynamic responses to active stand.
Briefly, participants will undergo active stand from supine to standing. After lying supine for 5 min, participants will be asked to stand as fast as they can. Beat-to-beat blood pressure and heart rate responses (assessed via the Finapres© NOVA) will be monitored during active stand and for three minutes after. To standardise assessments, all assessments are all taken at the same time each day, and all routine medications are taken as usual each morning. OH is defined by consensus as a sustained reduction of systolic blood pressure (SBP) of at least 20 mmHg or diastolic blood pressure (DBP) of 10 mmHg within 3 min of standing [43].
During active stand, cerebral oxygenation (TSI) will be estimated using NIRS-based analysis software. TSI analysis will be undertaken using the PortaLite OxySoft© NIRS device (PortaLite, Artinis Medical Systems B.V., Elst, The Netherlands) and the light emitting diode will be placed on clean skin on the right forehead, devoid of moisture or oil, and secured with a black headband. TSI readings are transferred via Bluetooth in real-time and will give an approximation of tissue oxygenation during rest, active stand, and all cognitive assessments.

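### The lead adverse-event comparison is one chi-square on an undivided count, so bradycardia, faints or hypotension outside the active stand, and serious events, have no safety analysis of their own

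*Protocol article*

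**What the plan says.** The abstract makes ascertainment of adverse events the main safety assessment and calls the haemodynamic measures a further one. The section on safety and tolerability sets the scope of recording: "Contemporaneous recording of any adverse events reported by participants whilst undergoing either active or sham stimulation". The Statistical analysis section then fixes the comparison: "To assess safety, a chi-square test will compare the number of adverse events reported during the active vs. sham condition". It states no split by type, severity or seriousness, although Table 1 of the article lists adverse and serious adverse events as assessed at visits 2 and 3.

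The same safety section gives the background rate: "The most common adverse events reported include local skin tingling, burning, redness, itching, tinnitus or headache which occur in up to 18% of participants". Pain, skin discomfort, tingling, headache and tinnitus are also captured by Likert questionnaires in both conditions, and the Statistical analysis section compares those scales as tolerability with paired statistics.

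The haemodynamic hazard has its own recording: "Detailed assessment of subjective (OH symptoms including faintness, light-headedness), peripheral (beat-to-beat blood pressure) and central (TSI) haemodynamic responses to active stand". It also has its own tests: "Further safety assessment will elicit symptoms experienced during active stand (using a chi-square statistic"), then "beat-to-beat blood pressure response to orthostasis – using mixed-effects linear regression with study condition as the independent variable", and a mixed model for TSI. Heart rate is monitored during the stand and for three minutes afterwards, but the Statistical analysis section names no safety analysis of heart rate or bradycardia. Heart rate variability is an exploratory aim.

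**The concern.** Sham uses the same device at the earlobe, so tingling, redness or itching can be expected in both conditions. If participants report these as adverse events, they enter the lead comparison as well as the Likert comparison, and each counts as much as a faint. The pooled result would then mainly describe skin and ear sensations.

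The events at stake are those that the separate tests do not reach: bradycardia at any time, a faint or a fall in blood pressure during stimulation but away from the active stand, and serious events. The only between-condition analysis stated for them is the pooled count. A non-significant result there says little about them, yet it is the first-named safety result.

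**Working it through.** **Inputs.** From the article: 40 participants, each measured under both conditions (Sample size, Study design), and local or sensory effects in up to 18% (Safety and tolerability of tVNS in MCI). The article gives no sham rate, no rate for other events and no significance level for this test, so there is no planned figure to reproduce. Assumptions: two-sided 5% level; local events equally frequent at both sites; other events under active stimulation only; the unit is a participant with at least one event, although the text speaks of the number of events.

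**1. Unpaired chi-square, as written.** With 40 per condition and a and b affected participants,

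X² = 80(a − b)² / [(a + b)(80 − a − b)],

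and the continuity-corrected form replaces (a − b)² by (|a − b| − 1)². Local reactors: 0.18 × 40 = 7.2, taken as 7 in each condition.

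| Active vs sham | X² | p | p, corrected |
|---|---|---|---|
| 10 vs 7 | 720/1071 = 0.67 | 0.41 | 0.58 |
| 12 vs 7 | 2000/1159 = 1.73 | 0.19 | 0.29 |
| 14 vs 7 | 3920/1239 = 3.16 | 0.075 | 0.13 |
| 15 vs 7 | 5120/1276 = 4.01 | 0.045 | 0.080 |
| 16 vs 7 | 6480/1311 = 4.94 | 0.026 | 0.048 |
| Other events alone, 4 vs 0 | 1280/304 = 4.21 | 0.040 | 0.12 |
| Other events alone, 6 vs 0 | 2880/444 = 6.49 | 0.011 | 0.034 |

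The pooled test needs 8 extra participants (9 corrected), or 20% to 22.5% of 40. Counted alone, other events need 4 (6 corrected).

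**2. Fewer local events.** With 4 local reactors per condition (10%), 11 vs 4 gives 3920/975 = 4.02, p = 0.045: 7 extra. With 2 per condition (5%), 8 vs 2 gives 2880/700 = 4.11, p = 0.043: 6 extra.

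**3. Power of the unpaired test** (exact enumeration). The pooled active rate is 1 − (1 − local)(1 − other); for 18% and 10% it is 1 − 0.82 × 0.90 = 0.262, against 0.18 under sham.

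| Other events, active vs sham | Alone | Pooled, 5% local | Pooled, 10% local | Pooled, 18% local |
|---|---|---|---|---|
| 10% vs 0% | 0.58 | 0.33 | 0.21 | 0.14 |
| 5% vs 0% | 0.14 | 0.14 | 0.10 | 0.08 |

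**4. Paired test (exact McNemar), which fits the crossover.** Other events alone: 6 vs 0 discordant gives p = 2 × 0.5⁶ = 0.031, and 5 vs 0 gives 0.063, so 6 are needed. Pooled, with the extra events among people who have no local reaction:

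- If the same 7 people react at both sites, they are concordant and drop out. The requirement stays at 6 vs 0, so nothing is lost.
- If the 7 reactors at each site are different people, the discordant counts are 7 + x vs 7. Then 17 vs 7 gives p = 0.064 and 18 vs 7 gives p = 0.043, so x = 11.

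A paired test therefore needs between 6 and 11 extra participants, depending on overlap. Another event in someone who also reacts locally at both sites is invisible to it.

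**5. What separation can and cannot do at 40.** The chance of seeing at least one event is 1 − 0.95⁴⁰ = 0.87 at a 5% rate and 1 − 0.99⁴⁰ = 0.33 at 1%. Zero of 40 leaves an exact two-sided 95% upper limit of 1 − 0.025^(1/40) = 8.8%. Power for 5% vs 0% is 0.14 by chi-square and 0.01 by McNemar, even with the events counted alone.

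**The case against.** A reader might infer that the trial could call stimulation safe on its lead test while the hazard it names goes undetected. The documents do not support that. The sentence after the adverse-event test adds separate comparisons of stand symptoms, blood pressure and TSI, and Table 1 lists the active stand with TSI under the primary safety outcome. Hypotension and faintness provoked by standing are not left to the pooled count. The article also describes the risk as a "theoretical risk of increasing cardiac vagal-mediated bradycardias or hypotensive episodes by stimulating the right VN", stimulates only the left ear, and excludes diagnosed arrhythmia and pacemakers. That lowers the expected event rate, but the Background says only that left-sided stimulation is less likely to cause bradycardia and still treats establishing safety as essential.

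A reader might also infer that a correct paired test would suffer the same dilution. That holds only so far as local reactions occur in different people at the two sites. If the same people react at both, which the shared device makes plausible, the paired requirement does not change.

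Finally, coding of events by type and seriousness, and individual listings, are commonly left to a full protocol or SAP that is not shown. Their absence is not the point here, and nothing in the article says that events will be reported only as a total. The point is that the one comparison the article does fix is on the undivided count. Likert scales already cover local sensations, but the article does not say that those sensations are kept out of the adverse-event count.

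**Conclusion.** The point holds in a limited form. The stated adverse-event comparison gives expected local or sensory effects the same weight as systemic or serious events. For bradycardia, for faints or hypotension away from the active stand, and for serious events, the article names no other safety analysis.

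The requirement of 8 to 9 extra participants is illustrative. It rests on 18% local events in each condition, where 18% is the article's upper figure and equal sham frequency is assumed, and on an unpaired test of participants. It falls to 6 at 5% local events, and also to 6 under a paired test with complete overlap of local reactors, where pooling costs nothing. At a 10% rate of other events the unpaired loss of power persists across the local rates tried; at 5% for both there is essentially none. This is a cheap improvement to the stated analysis, not a flaw that undermines the trial.

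**What to change.** Before data are seen, classify every adverse event as local/sensory (effects at the electrode, headache, tinnitus) or other, and mark serious events.

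- Report local/sensory events with the tolerability results.
- Report other events, and serious events, as the number of participants with at least one event under active and under sham, each with an exact 95% confidence interval, and list every such event individually. Show bradycardia, hypotension and faints outside the stand as named lines.
- State that the safety conclusion will not rest on a non-significant p-value for the pooled count.

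The cost is a sentence or two in the analysis section and a code on the adverse-event form. The downside is that the main safety result will rest on few events with wide intervals (0 of 40 is compatible with a rate up to 8.8%), and there is no useful power for rare events at this size. That is why estimates and listings are proposed and not a further significance test.

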**Fig. 1 Fig1:**
[figure not shown]
Method of crossover

Our study will follow the Standard Protocol Items: recommendations for Interventional Trials (SPIRIT) guidelines [41]. Table 1 illustrates the SPIRIT flow diagram summarising study procedures, outcome measures, randomisation and assessments for each study visit.

**Table 1 Tab1:** Flowchart of VINCI-AD Protocol Timeline

			Study Period					
			Screening (day − 90 to day − 7)	Visit 1 (day 0)		Visit 2 (day 7–10)		Visit 3 (day 14–17)
Enrolment								
- Eligibility Screen			x					
- Informed Consent			x					
Intervention								
- Baseline assessments (no stimulation)				x				
- Active (left cymba conchae) stimulation						ø		ø
- Sham (left earlobe) stimulation						†		†
Assessments								
- General assessment, vitals, medication changes				x		x		x
- Primary Outcome: Safety								
- Assess for AE/ SAEs						x		x
- Active stand with TSI				x		x		x
- Primary Outcome: Acceptability and Tolerability								
- Likert scale questionnaires						x		x
- Cognitive assessments								
- FNAT				x		x		x
- SART				x		x		x
- SHQ				x		x		x
- Verbal word learning				x		x		x
- Semantic fluency				x		x		x
- Digit span forwards				x		x		x
- Digit span backwards				x		x		x
- Verbal word recall				x		x		x
- Verbal word recognition				x		x		x
- Frontal Oxygenation								
- Cognitive testing TSI				x		x		x
- Neurocardiovascular assessments								
- HRV				x		x		x
- Serum / Plasma venepuncture								
- Inflammatory cytokine panel				x		x		x
- Device usability assessment								
- Kettle test								x

Ø = active stimulation randomisation: participant randomised to either sham or active stimulation at Visit 2 and alternative stimulation site at Visit 3

† = sham stimulation randomisation: participant randomised to either sham or active stimulation at Visit 2 and alternative stimulation site at Visit 3

AE – Adverse event; SAE – Serious adverse event; FNAT – Face Name Association Task; SART – Sustained Attention Response Task; SHQ – Sea Hero Quest Tas; NIRS – functional Near Infrared Spectroscopy; HRV – Heart Rate Variability; TSI – Tissue Saturation Index

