### Intervention

Participants will receive active and sham stimulation with the NEMOS © CerboMed tVNS device. Two small electrodes emit a low-voltage electric signal which permeates the skin. When the electrodes are placed at the cymba conchae of the ear, stimulation actives the afferent branch of the VN that innervates the skin of the ear (Arnold’s nerve). The electric signal consists of an 8 Hz frequency wave with participant-selected amplitudes ranging from 0.1 mA to 5 mA depending on their sensory threshold, the signal cycles of 200 ns and comes in 30 s on – 30 s off bursts. For the sham condition the electrode is placed on the earlobe which is free of vagus innervation. For the active condition it is placed on the cymba conchae of the left ear. At each stimulation study visit the device is explained to the participant and then fitted by the study researcher. Participants are given oral and written instructions at each stimulation study visit regarding how to set up and fit the device in their ear.

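### The only named adverse-event analysis contrasts active with sham stimulation from the same device, so it cannot show how often tVNS causes adverse events in MCI

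*Protocol article*

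**What the plan says.** The Statistical analysis section of the protocol article makes safety and feasibility the primary aim. Its one named analysis of adverse events is a chi-square test to "compare the number of adverse events reported during the active vs. sham condition". The Likert tolerability scales are compared between active and sham with a paired test. No acceptable rate, margin or rule for reading either result is given.

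The Intervention section says "Participants will receive active and sham stimulation with the NEMOS © CerboMed tVNS device", and then: "For the sham condition the electrode is placed on the earlobe which is free of vagus innervation". Table 1 lists "Sham (left earlobe) stimulation", and its footnote has each "participant randomised to either sham or active stimulation at Visit 2 and alternative stimulation site at Visit 3". Only the electrode site is described as differing.

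The section on safety and tolerability expects "local skin tingling, burning, redness, itching, tinnitus or headache which occur in up to 18% of participants". Table 1 schedules adverse-event assessment and the Likert scales at Visits 2 and 3 only. It schedules the active stand with TSI at all three visits.

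The Sample size section sets 40 participants by reference to earlier tVNS studies, without a power, effect-size or precision statement.

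**The concern.** Four of the six effects the article expects (tingling, burning, redness, itching) are local responses of skin to stimulation and can arise at the earlobe as well as at the cymba conchae. A comparison between the two sites removes whatever they share. What remains is the extra effect of the vagal site. The aim also asks something else: how often older adults with MCI have adverse events when they use this device.

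If the test is the main adverse-event result, a trial with frequent skin effects in both conditions and a trial with almost none would usually report the same thing, no significant difference. With 40 participants, a real excess under active stimulation could also be missed.

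**Working it through.** **Inputs from the article.** 40 participants in a crossover, so 40 per condition if all complete; reference adverse-event rate up to 18%; chi-square test, active against sham.

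**Assumptions not in the article.** Two-sided alpha 0.05; chi-square without continuity correction; outcome taken as whether a participant had at least one event; within-person correlation (phi) of 0, 0.3 or 0.5; a sham rate of 9% for the power example; rates of 30% and 50% as illustrations. The article gives no power or precision figure for safety, so there is none to reproduce.

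**Test statistic.** X² = (pA − pS)² / [2·p̄(1 − p̄)/40], where pA and pS are the observed proportions and p̄ is their mean; reject if X² > 3.84. Probabilities come from summing over all possible sets of 40 pairs, with P(event in both) = πAπS + phi·√[πA(1 − πA)πS(1 − πS)], where πA and πS are the true rates.

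**Step 1: both sites cause events at the same rate.** Probability of a non-significant result:

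| True rate in both | phi 0 | phi 0.3 | phi 0.5 |
|---|---|---|---|
| 18% | 94.8% | 97.9% | 99.3% |
| 30% | 95.2% | 98.1% | 99.4% |
| 50% | 94.3% | 97.7% | 99.3% |

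The columns barely move as the rate rises from 18% to 50%, so the test carries almost no information on the absolute rate.

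The rise from left to right comes from ignoring the pairing. The true variance of the difference is 2p(1 − p)(1 − phi)/40, but the unpaired test uses 2p(1 − p)/40. At p = 0.18 and phi = 0.5 the true standard error is √(2 × 0.1476 × 0.5/40) = 0.061, while the test uses √(2 × 0.1476/40) = 0.086. A nominal 1.96 therefore becomes 1.96 × 0.086/0.061 ≈ 2.8 true standard errors.

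**Step 2: active doubles the sham rate (18% against 9%).** With phi = 0.3, P(event in both) = 0.18 × 0.09 + 0.3 × √(0.1476 × 0.0819) = 0.0162 + 0.0330 = 0.0492. Power is 18% at phi 0.3 and 15% at phi 0.5. With no correlation it is 23%. Continuity correction lowers each of these.

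**Step 3: what 40 participants can support.** Exact (Clopper–Pearson) 95% limits for the proportion with at least one event under active stimulation:

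- 0/40: upper limit 1 − 0.025^(1/40) = 8.8%.
- 2/40 (5%): 0.6% to 16.9%.
- 7/40 (17.5%, close to the cited 18%): 7.3% to 32.8%.

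**Likert scales.** No simulation is needed. If sham raises a score by the same amount as active, the within-person difference has mean zero however large that amount is.

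**The case against.** The strongest defence is that the contrast is deliberate. The Background and the safety section identify vagally mediated bradycardia, hypotension and reduced cerebral perfusion as the concern particular to this population. An earlobe comparator without vagal innervation isolates exactly that. This stands, and it is why the active–sham comparison should be kept. It does not supply the rate of adverse events under active stimulation.

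A reader might infer that the article treats a non-significant test as proof of safety. It does not say so. It says events will be compared and safety reported. The weakness is that no absolute result and no reading rule is named beside the test.

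A reader might also infer that safety as a whole lacks an unstimulated comparator. That is not so: active-stand blood pressure and TSI are measured at Visit 1. Only adverse events and the Likert scales are not.

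Nor should the statement "All participants will be included in final analysis" be read as placing people who never received a condition in its adverse-event denominator. The article states no such denominator, and events are recorded while a condition is being delivered.

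Per-condition counts must exist to run the chi-square, and the article promises descriptive proportions for the cohort. Detailed tables may properly sit in an analysis plan. That answers a complaint about missing detail, but not one about which result is put forward as the safety analysis.

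Finally, current during sham is inferred from the descriptions of sham stimulation and an alternative stimulation site; no sham current setting is stated.

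**Conclusion.** The point holds for adverse events and Likert local side effects. As written, the only named analysis of these outcomes answers whether the vagal site adds to the effects of stimulating the ear, not how often tVNS causes adverse events in MCI. With equal rates at both sites the chi-square is non-significant about 95% of the time, or 98–99% with phi of 0.3–0.5, across true rates of 18% to 50%. A non-significant result would not be evidence of safety either: power is about 15–18% for 18% against 9% at those correlations.

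These figures assume two-sided alpha 0.05, no continuity correction, 40 complete pairs and one binary outcome per participant and condition. The 9% sham rate and the phi values are illustrative; only the 18% comes from the article. The conclusion that shared effects cancel does not depend on them, but does depend on sham delivering current.

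**What to change.** - **Main adverse-event result:** the proportion of participants with at least one adverse event during active stimulation, with exact 95% interval, among those who received active stimulation.
- **Alongside it:** the same summary for sham and for either stimulation. For the Likert side effects, report the level in each condition as well as the difference.
- **Supportive:** replace the unpaired chi-square with a paired active–sham difference in proportions and its confidence interval. This respects the crossover but will not cure the small sample, so the interval matters more than the p-value.
- **Reading rule:** state that a non-significant active–sham difference is not evidence of safety.
- **Optional:** record the same symptom prompts at Visit 1. This would give a background rate for non-local symptoms such as headache and tinnitus. It adds little for skin effects, and Visit 1 always comes first, so condition and order cannot be separated there.

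The cost is a change of analysis wording and, if the option is taken, a few minutes of an existing form at Visit 1. The downside is that the safety statement becomes a rate with a wide interval rather than a p-value.
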